#### Sensitivity analysis

We will perform extensive one-way and multi-way sensitivity analyses to evaluate the key drivers of impact, cost, and cost-effectiveness in the Indian context and will perform probabilistic uncertainty analyses to quantify the level of uncertainty in our cost-effectiveness estimates.

### Objective 4: analyses

The degree of lung impairment in TB cases will be assessed by comparing with apparently healthy controls with no evidence of TB disease. Lung function parameters will be z-score standardized using Global Lung Initiative (GLI) reference equations [95]. Impaired lung function parameters will be defined as having an observed parameter value <5th percentile of the expected parameter distribution for a given age, sex, and height using the GLI equations. We will measure the association between impaired FEV1, FVC and FEV1/FVC ratio, and TB recurrence using Poisson regression. Our secondary analysis will measure the association between change in respiratory questionnaire scores and lung function parameters during follow-up, and subsequent TB recurrence using mixed-effects Poisson regression.

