### Sample size {14}

The sample size for index patients (*n* = 1076) includes 538 in the HACF arm and 538 in the TACF arm (1:1 ratio). On average, we will enroll two HHCs per index patient (*n* = 2152). The total estimated sample size for index patients and HHCs is 3228 individuals.

Data from relevant studies suggest that 10–13% of index patients will develop recurrent TB in each arm [21, 22] and an additional 1–2% of HHCs will develop TB during the study period [58]. Assuming a rate of 12 TB cases per 100 person-years among index patients and 1 TB case per 100 person-years among HHCs, we are powered at 80% to determine that the TACF arm is non-inferior to the HACF arm with a non-inferiority interval of 3 per 100 person-years and a sample size of 1076 index patients and two HHCs per index patient (*n* = 2152). This sample size for the primary outcome is adjusted for 10% projected losses to follow-up. For the secondary outcome, we anticipate that 10% (215/2152) of HHCs will be children < 6 years of age. Data from Pune suggest that approximately 30% of child contacts will have been screened for TB and either initiated on TB therapy or TPT [59]. Thus, we anticipate 70 eligible children in each study arm and hypothesize > 60% to be screened and initiated on TB therapy or TPT in the HACF arm and less than 20% in the TACF arm. We will have at least 90% power to see a difference of 60% vs 20% and 80% power to see a difference of 50% vs 25%.

For objective 2, we will conduct a total of 40 in-depth interviews with index patients (20 with and 20 without recurrent TB) and one HHC for each patient (40 total). We will also interview 20 HCWs to achieve a total sample size of 100. We will use purposive sampling to obtain a maximum variation sample by study arm, as well as gender and age group for index patients, HHCs, and a range of HCW types and levels.

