#### Objective 4: data collection

We will measure lung function and respiratory health status at enrolment and month 18 (“mop-up”) in all participants and semi-annually in the home-based arm only. Lung function will be assessed by point-of-care pre-bronchodilator spirometry performed by trained study staff according to American Thoracic Society and European Respiratory Society guidelines [75]. We will collect key lung function indices such as forced expiratory volume in the 1st second (FEV1), forced vital capacity (FVC), and peak expiratory flow rate (PEF) at enrolment and follow-up. Additionally, we will measure respiratory health status and quality of life from the patient perspective using standardized questionnaires such as the Saint Georges Respiratory Questionnaire and the COPD Assessment Test [76–78].

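### Objective 4 asks about severity of lung impairment, but the stated recurrence model uses a two-level exposure and gives no severity gradient

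*Protocol article*

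**What the plan says.** Objectives {7} lists, as the fourth objective, measuring how the severity, chronicity and progression of post-TB lung impairment relate to recurrent TB. Severity is named first.

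The section Objective 4: analyses then states, in this order:

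- A comparison with controls: "The degree of lung impairment in TB cases will be assessed by comparing with apparently healthy controls with no evidence of TB disease".
- Standardisation: "Lung function parameters will be z-score standardized using Global Lung Initiative (GLI) reference equations".
- A definition, with expected values specific to the person's age, sex and height: "Impaired lung function parameters will be defined as having an observed parameter value <5th percentile of the expected parameter distribution".
- The recurrence model: "We will measure the association between impaired FEV1, FVC and FEV1/FVC ratio, and TB recurrence using Poisson regression".
- A further model: "Our secondary analysis will measure the association between change in respiratory questionnaire scores and lung function parameters during follow-up, and subsequent TB recurrence", by mixed-effects Poisson regression.

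Elsewhere, Statistical methods for primary and secondary outcomes {20a} includes respiratory impairment in a list of risk factors for recurrent and new TB, without saying how it is coded. Table 1 and Objective 4: data collection place spirometry of index patients at entry and month 18 in both arms, and additionally at months 6 and 12 in the home-based arm only.

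**The concern.** The exposure in the stated recurrence model is a state that is either present or absent. With the cut at the reference 5th percentile (z = -1.645), a patient at z = -1.7 and one at z = -4 are coded alike, while patients at z = -1.6 and z = -1.7 are coded as opposites. Such a term yields one rate ratio per index. It cannot show whether recurrence rises with worsening lung function, which is what severity means in the objective.

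Two things are at stake. The reported result would not match the objective's first-named target. Precision would also be lost in an analysis with a limited number of recurrences, although the continuous measure is already being derived.

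**Working it through.** **1. Does any stated analysis give a gradient of recurrence over baseline severity?**

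| Stated analysis | Exposure | Outcome | Baseline severity gradient? |
|---|---|---|---|
| Degree of impairment against controls | TB case or healthy control | Lung function | No; recurrence is not the outcome |
| Poisson model, Objective 4: analyses | Below 5th percentile or not | Recurrence | No; two levels |
| Secondary analysis, same section | Most naturally, change during follow-up | Later recurrence | No; this is progression |
| Risk-factor model, section {20a} | Respiratory impairment, coding not given | Recurrent and new TB | Not clearly |

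The visit schedule matters here. Before month 18, the telephonic arm has spirometry at entry only. Entry spirometry is therefore the only scheduled measure before month 18 that exists in both arms.

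**2. Expected recurrences.** The article gives no sample size, power or effect size for objective 4, so there is no figure to reproduce. The inputs come from Sample size {14}: the index-patient sample "includes 538 in the HACF arm and 538 in the TACF arm (1:1 ratio"), 1076 in all; the rate, "Assuming a rate of 12 TB cases per 100 person-years among index patients and 1 TB case per 100 person-years among HHCs"; and 10% loss to follow-up. Over one year each, with those lost contributing no time:

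1076 × 0.90 × 0.12 = 116.2, or about 116.

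Ignoring the loss gives 1076 × 0.12 = 129. The same rate carried to month 18 gives 116.2 × 1.5 = 174.

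**3. Information kept by the split.** For a normal exposure with a log-linear effect, cut so that a proportion p is impaired, the fraction kept relative to the continuous exposure is φ(c)² / [p(1 − p)], where c is the standard normal quantile of p and φ is the normal density. The prevalence p is an assumption.

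| Assumed p | Fraction kept | Fraction lost | Equivalent recurrences out of 116 |
|---|---|---|---|
| 50% | 0.637 | 0.363 | 74 |
| 30% | 0.576 | 0.424 | 67 |
| 20% | 0.490 | 0.510 | 57 |
| 10% | 0.342 | 0.658 | 40 |

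The last column is 116.2 × fraction kept. The fractions do not depend on the number of events, so longer follow-up leaves them unchanged.

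**4. What this means for power, as an illustration.** Assume a rate ratio of 1.30 per SD lower and 116.2 events. Approximate power is Φ(ln RR × √(events × fraction kept) − 1.96).

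- Continuous: 0.262 × √116.2 = 2.83, so Φ(0.87) = 81%.
- Two-level: 62% at p = 50%, 57% at 30%, 51% at 20%, 38% at 10%.

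A simulation (968 patients, 12 per 100 person-years, 1000 replicates, Poisson regression on the z-score and on z < -1.645) gave 76–82% continuous and 57–62% two-level at prevalences of 20–50%. At 5% prevalence the formula gave 27% and the simulation 38%, so the formula overstates the loss when few patients are impaired. The direction and rough size agree over 20–50%.

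**The case against.** The strongest reply is that this is one paragraph of a condensed journal article. How a covariate enters a regression is often settled in a full protocol or analysis plan that is not shown. The article does not say that z-scores serve only to form a yes/no variable. This stands in part: a reader might infer that no graded analysis will ever be done, or that the severity part of the objective cannot be answered, and the article supports neither. The z-scores are kept, and a graded model could be run at any time. What the reply does not remove is that the two-level coding is stated, directly before the model that uses it, and does not fit the objective's wording.

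Second, the secondary analysis could be read as change in questionnaire scores together with repeated levels of lung function. That reading is possible but less natural. Even so, before month 18 repeated levels are scheduled only in the home-based arm.

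Third, section {20a} also models respiratory impairment, and its coding is open. This is correct, and it is why the claim is limited to no other analysis clearly giving a gradient.

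Fourth, the size rests on a prevalence, normality and log-linearity that the article does not give, and a true threshold at the cut would reduce the loss. This stands. A spline would reveal a threshold, whereas a two-level term cannot test for one.

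Fifth, the word main does not appear; it is inferred from the next sentence, which introduces the secondary analysis. Finally, objective 4 is an observational association outside the primary and secondary outcomes and carries no power claim. That limits the weight of the point.

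**Conclusion.** The point holds as a mismatch between a stated objective and the model stated for it. The recurrence model gives a two-level contrast for FEV1, FVC and FEV1/FVC, not a severity gradient, and no other stated analysis clearly supplies one for baseline lung function.

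Under rough normality and a log-linear effect, the split keeps about 64% to 34% of the information over assumed impairment prevalences of 50% to 10%. About 116 recurrences are expected in 12 months after the stated loss, and more by month 18. The power figures rest additionally on an assumed rate ratio and are illustrative only.

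A reader might also take this as a flaw in the trial's main comparison. It is not: the non-inferiority analysis does not use lung function as its exposure. Nor does the point bear on who is referred for lung impairment. Relevant concomitant care {11d} does not tie referral to the 5th percentile, and nothing is recommended here on that. It is a worthwhile correction to a non-primary objective.

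**What to change.** In Objective 4: analyses, name the entry GLI z-scores for FEV1, FVC and FEV1/FVC, entered continuously, as the main exposure in the Poisson model for recurrence. Report the rate ratio per 1 z-score lower, with a spline check for non-linearity. Keep the below-5th-percentile contrast as a supportive analysis. The secondary analysis of change can stay as it is for progression.

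The cost is a change of wording and a little more analysis. The z-scores are already to be derived, and no visit, measurement or participant is added. The one drawback is that a rate ratio per z-score is less directly tied to a clinical category, which the retained supportive contrast covers.

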### Methods in analysis to handle protocol non-adherence and any statistical methods to handle missing data {20c}

All deviations from the protocol will be addressed in the study participant’s source documents.

### Plans to give access to the full protocol, participant level-data and statistical code {31c}

The final de-identified trial dataset and statistical code will be made available by the corresponding author on reasonable request.

### Oversight and monitoring

#### Composition of the coordinating center and trial steering committee {5d}

Dr. D.Y. Patil Medical College, Hospital and Research Centre, Dr. D.Y. Patil Vidyapeeth, located in the Pimpri-Chinchwad Municipal Corporation area of Pune district, India, serves as the coordinating center running day-to-day trial operations with organizational and scientific support from JHU located in Baltimore, Maryland. JHU also serves as the coordinating center for regulatory tracking specifically. A core group of study coordinators and investigators meets at least biweekly. The Maharashtra State TB Office oversees the trial, with formal meetings held at least annually.

#### Composition of the data monitoring committee, its role and reporting structure {21a}

N/A. A data monitoring committee was not included for TB Aftermath, as the trial is a hybrid effectiveness-implementation trial with minimal risk to participants, and the activities included are an extension of usual care by HCWs.

#### Adverse event reporting and harms {22}

N/A. There is no more than minimal risk associated with study procedures for any of the objectives and thus, adverse events are not anticipated.

#### Frequency and plans for auditing trial conduct {23}

During the study period, an internal monitor will review trial conduct on an annual basis. The internal monitor is an employee of Johns Hopkins India who is not otherwise involved in the conduct of the trial.

#### Plans for communicating important protocol amendments to relevant parties (e.g., trial participants, ethical committees) {25}

If a protocol deviation meets the following criteria, it will be reported to the IRB and the sponsor: (1) results in a significant added risk to the study participant occurs when the participant or investigator has failed to adhere to protocol requirements impacting on enrolment eligibility, safety surveillance, and endpoint outcomes and (2) when there is non-adherence to Good Clinical Practice standards. Examples of reportable protocol deviations include eligibility violations, informed consent violations, and confidentiality violations. Furthermore, protocol deviations that violate eligibility criteria, informed consent processes, or participant confidentiality must be reported immediately to the local IRB, per their requirements. All other protocol deviations (those that do not meet the criteria outlined above) will be maintained in a log that is submitted to the IRB with annual progress reports.

#### Dissemination plans {31a}

Study results will be disseminated between years 3 and 5 of the study. Meetings will be held with NTEP officials to share results and discuss policy implications. Materials and/or publications generated under the project will be disseminated in accordance with the participating institution and NIH policies.

## Discussion

Implementing ACF is a recognized need for TB control in high incidence settings. However, the comparative effectiveness of ACF strategies among treated TB patients has not been assessed despite the high risk of recurrence among this populations and the high rate of TB among their HHCs. Using a hybrid effectiveness-implementation approach and collaborating with the Indian NTEP will allow for rapid scale-up of the strategy(ies) deemed to be successful. To strengthen generalizability of results, our study is embedded into the program and utilizes existing NTEP HCWs. Additionally, measuring the costs and cost-effectiveness of these strategies and assessing risk factors for recurrence will provide insight into prioritization of subpopulations when ACF for treated TB patients is implemented. This novel trial will guide India’s scale-up of post-treatment ACF and provide an evidence base for designing strategies to detect recurrent and new TB in other high burden settings.

## Trial status

This paper corresponds with protocol version 1.3, January 28, 2022. Recruitment began on January 29, 2021, and the approximate completion date for recruitment is February 1, 2023.

## Data Availability

The final de-identified trial dataset will be made available by the corresponding author on reasonable request.

## Abbreviations

ACF: Active case finding
AUDIT: Alcohol Use Disorder Identification Test
DALY: Disability-adjusted life years
DOT: Directly observed therapy
eCRF: Electronic case report form
HCW: Health care worker
HH: Household
HACF: Home-based active case finding
HHC: Household contacts
HIV: Human immunodeficiency virus
IRB: Institutional Review Board
JHU: Johns Hopkins University
NIAID: National Institute of Allergy and Infectious Diseases
NIH: National Institutes of Health
NTP: National Tuberculosis Program
NTEP: National Tuberculosis Elimination Program
PI: Principal investigator
RE-AIM: Reach, Effectiveness, Adoption & Acceptability, Implementation, Maintenance
STLS: Senior TB laboratory supervisor (STLS)
STS: Senior TB treatment supervisor
TACF: Telephonic active case finding
TB: Tuberculosis
TPT: Tuberculosis preventive treatment
TU: Tuberculosis unit
WHO: World Health Organization
